**Figure 1 Fig1:**
[figure not shown]
**The Books Beyond Words intervention.**

#### How the Books Beyond Words intervention will be used

After giving consent and completing the baseline questionnaires, patients in the intervention condition will use the booklet with the research nurse and carer, in a quiet room at the epilepsy clinic. The nurse will go through the booklet with each patient at their own pace. Health professionals and carers can create their own story with the patient or use the story provided at the end of the booklet. The booklet contains instructions for use and a list of useful resources and services. The research nurse will show the first picture of the booklet to the person with learning disabilities, who should be encouraged to hold the book and turn the pages at their own pace. Depending on the patient’s communication abilities and reactions, it is advised that the research nurse will prompt them to say what is happening, whether this has happened to them before, and how they feel about it. We anticipate that it may take up to one hour to go through the booklet. If the intervention cannot be explored in one sitting, the research nurse will arrange a further appointment. The patient will also be given a copy to take home and explore with the carer and/or relatives.

It is recommended that the patient is given the opportunity to use the book at least twice more at home over the study duration. The research nurse will call each carer two weeks after randomization to remind them that the patient should be given opportunities to use the booklet at least twice more. Use of the book at home with the carer or other relatives will be monitored as part of the follow-up assessments. The carers will not receive any formal training in using the booklet, but will be able to watch an online video and training slides explaining how to use the book with the person they care for. A link to the training video and slides will be provided by the nurse at the end of the initial meeting. The research nurse will receive a half-day training course in using the intervention.

### Control group

Participants in the control group will receive routine information and services. The use of a picture book, such as the Books Beyond Words intervention or other educational package, will not be part of the routine consultation. After the study has terminated, patients in the control condition will be provided with a Books Beyond Words booklet to use with the epilepsy nurse specialist, the consultant and/or the carer.

### Outcome measures

Each patient will be assessed at baseline (T0), and at four (T1), 12 (T2) and 20 (T3) weeks after randomization (see Figure 2.). We will measure the following outcomes for both groups except where specified otherwise (see Table 1).

**Figure 2 Fig2:**
[figure not shown]
**Consolidated Standards of Reporting Trials (CONSORT) study flow-chart.**

**Table 1 Tab1:** **Study procedures according to study schedule**

Study procedures	Study period				
	Enrollment	Randomization	Post-randomization		
		T0	T1 week 4	T2 week 12	T3 week 20
**Eligibility screen**	X				
**Informed consent**	X				
**Allocation**		X			
**Intervention**		X			
**Rates of recruitment**		X	X	X	X
**Quality of life** (Epilepsy and Learning Disabilities Quality of Life, ELDQOL. scale)		X	X	X	X
**Demographic data**		X			
**Seizure severity** (using ELDQOL Seizure Severity Scale)		X			
**Seizure control** (diary cards)		X	X	X	X
**Feasibility and acceptability** (qualitative interviews)					X
**Resource use**		X			X
**Quality of life** (EQ-5D-5L scale)		X	X	X	X

#### Quantitative assessment

The quantitative assessment will examine the following:Number of eligible patients identified and number recruited.Variability of the primary outcome quality of life, using the Epilepsy and Learning Disabilities Quality of Life (ELDQOL) scale [29, 30]. The ELDQOL consists of four subscales: behaviour, seizure severity, mood and side effects.Seizure control as a secondary outcome measure, assessed using a seizure diary.Seizure severity as a secondary outcome measure, assessed using the seizure severity subscale of the ELDQOL scale.Discontinuation rates across both arms and reasons.Patterns of use of the Books Beyond Words booklet (for intervention group only).Use of other epilepsy-related information.Resource use and health-related quality of life using a context-specific resource use questionnaire and the EQ-5D-5 L scale [31].Demographic data: age, sex, ethnicity, and living circumstances of the participant, information about the type of care provided by the carer and relationship to the participant.

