#### Exclusion criteria

The exclusion criteria for this study are as follows:Vision impairment.Confirmed diagnosis of dementia.Have used the Books Beyond Words booklet for epilepsy in the past 12 months.

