### Data analysis

#### Quantitative data

The analysis primarily aims to determine the feasibility of undertaking a full-scale randomized controlled trial and will seek to assess:The number and demographics of eligible patients identified, screened, consented and randomized to each arm, and the relative performance in each clinic.The demographics of patients who are excluded from the trial, reasons for exclusion and estimation of the proportion of eligible patients approached who agree to enter and complete the trial.The proportion of completed study measures in each arm, measured from baseline to the last follow-up assessment.The proportion of patients withdrawing from the study, measured from baseline to the last follow-up assessment.The variation in the primary outcome measure that will be used, following Cocks and Torgerson [32], to determine whether a one-sided 80% confidence interval would exclude a 10% increase in the primary outcome (ELDQOL).The frequency of use of the Books Beyond Words intervention, and other sources of information before and after randomization, and the extent to which use of the Books Beyond Words booklet influences outcome and other information resource use.

In parallel, a health economic assessment will be undertaken. We will monitor levels of resource-use and quality of life to inform the decision as to how costs and benefits should be measured as part of a future, more definitive study. NICE guidance recommends that costs are calculated from the perspective of the NHS and Personal Social Services (PSS) [33]. We will thereby seek to monitor levels of resource-use associated with the epilepsy booklet and the use of other NHS and PSS resource-items. Appropriate unit costs will subsequently be attached to all items of resource-use, to estimate the mean overall cost in each study-arm [34]. In line with NICE guidance, the EQ-5D [35] will be used to assess the effectiveness of each option. This will enable the quality-adjusted life year gain to be estimated. All analyses will be reported according to relevant CONSORT standards [36].

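### Booklet use is recorded in the intervention group only, so control use is not counted and the planned use–outcome analysis cannot support a statement of influence

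*Protocol article*

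**What the plan says.** The Outcome measures section sets a default: "We will measure the following outcomes for both groups except where specified otherwise (see Table 1"). The Quantitative assessment list then makes an explicit exception: "Patterns of use of the Books Beyond Words booklet (for intervention group only"). The neighbouring item, "Use of other epilepsy-related information", carries no such restriction, so by the default it applies to both groups. Table 1 does not settle the matter, because it has no row for either item.

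The Quantitative data section under Data analysis plans to assess "The frequency of use of the Books Beyond Words intervention, and other sources of information before and after randomization". Its second aim in the same item is to establish "the extent to which use of the Books Beyond Words booklet influences outcome and other information resource use". It names neither an arm nor a method.

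Two provisions limit control exposure. One is an exclusion at entry: "Have used the Books Beyond Words booklet for epilepsy in the past 12 months". The other concerns routine care: "The use of a picture book, such as the Books Beyond Words intervention or other educational package, will not be part of the routine consultation". For the intervention group, the section on how the booklet will be used adds: "Use of the book at home with the carer or other relatives will be monitored as part of the follow-up assessments".

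**The concern.** The two sections do not match. One restricts collection of booklet use to a single arm; the other analyses it without that restriction.

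The restriction matters for two reasons.

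- **Control exposure.** The booklet already exists outside the trial, as the prior-use exclusion shows. Patients are randomized individually within five clinics of one trust, and intervention patients take a copy home. The entry exclusion looks backwards, and the control-group statement covers the consultation only. Neither measures what controls use during the 20 weeks. How often controls obtain the booklet is one of the design inputs that a study of methodological and design issues could usefully supply.
- **Use and outcome.** If frequency of use is known in the intervention arm only, relating it to outcome compares heavier with lighter users within that arm. Randomization does not protect that comparison. Carer engagement, patient ability or seizure burden could affect both how often the booklet is opened and how the quality-of-life scale is completed.

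**Working it through.** **1. What counts control use.** Setting the sources side by side:

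| Source | Arms | Counts booklet use in controls? |
|---|---|---|
| Patterns of booklet use (Quantitative assessment) | Intervention only | No |
| Use of other epilepsy information (Quantitative assessment) | Both, by the default rule | Not designed to; a carer might mention the booklet |
| Week-20 interviews (Qualitative assessment) | Sample of 15 patients and carers from both groups, plus nine health professionals | Might reveal cases; gives no rate |
| Frequency of use (Data analysis) | No limit stated | An analysis item that the restricted collection cannot supply for controls |

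**2. Number of patients available.** The Sample size section takes 9% of 174 per group: 0.09 × 174 = 15.66, rounded up to 16, which reproduces the stated figure. The target is 20 per group with 25% dropout, and 20 × 0.75 = 15. So 15 to 20 patients per arm is the working range.

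**3. Precision of a use–outcome relation in one arm.** For an illustrative correlation r = 0.3 (assumed), the Fisher interval is tanh(atanh(0.3) ± 1.96/√(n − 3)):

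- n = 15: -0.25 to 0.70
- n = 20: -0.16 to 0.66

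These intervals show imprecision only. The confounding argument is separate and rests on home use being discretionary and on the carer completing the follow-up questionnaires.

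**4. What asking controls would deliver.** The chance of seeing at least one exposed control is 1 − (1 − c)^n, for an assumed true exposure c:

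| c | n = 20 | n = 15 |
|---|---|---|
| 5% | 0.64 | 0.54 |
| 10% | 0.88 | 0.79 |
| 20% | 0.99 | 0.96 |

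If no control is exposed, the one-sided 95% upper limit is 1 − 0.05^(1/n): 14% for 0 of 20 and 18% for 0 of 15. For comparison, if about 7 of the 15 interviewed were controls (assumed), 0 of 7 would give 1 − 0.05^(1/7) = 35%.

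**5. Illustrative effect on the full trial.** If a fraction c of controls obtains the full effect, the difference shrinks by (1 − c) and the sample size grows by 1/(1 − c)²:

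- c = 5%: 174/0.9025 = 193
- c = 10%: 174/0.81 = 215
- c = 20%: 174/0.64 = 272

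The documents give no exposure rate, so these rows show scale only.

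**The case against.** The strongest reply is that the restricted item is an adherence check. The protocol recommends at least two further uses at home and monitors them, which makes sense only for patients who were given the booklet. The exact wording of the other-information item may sit in forms that a journal article does not show. The article also says that these booklets are not routinely adopted in the NHS, and controls receive theirs only after the study, so exposure may be low. Even a perfect result leaves room for doubt: 0 of 20 still allows 14%, which by the formula above gives about 174/0.86² = 235. This much stands: the size of the problem is unknown, and the remedy yields an imprecise estimate. It does not remove the mismatch between the two sections, nor does it supply a count in controls.

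A reader might go further and infer three things that the documents do not support:

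- **That contamination cannot be seen at all.** The other-information item and the interviews could reveal cases. The accurate statement is that control use is not counted.
- **That the plan specifies a confounded within-arm analysis.** No method is named, and adjustment may be set out in an analysis plan not shown. The within-arm reading is an inference, although it is the only comparison of use frequency that data collected in one arm would allow. It is also possible to attach the before-and-after wording to other information sources alone.
- **That contamination decides between individual and cluster randomization, or that a positive association would be misread as a dose effect.** The documents do not pose that design choice. They also say that the analysis is primarily about feasibility and that the study will not demonstrate whether the intervention achieves its goals.

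**Conclusion.** The point holds as a modest, inexpensive improvement. The restriction of booklet use to one arm is an explicit choice, it sits uneasily with the unrestricted analysis item, and it leaves control use without a count. With use frequency known in about 15 to 20 intervention patients, self-selected home use and carer-completed outcomes, the planned analysis cannot support a statement that use influences outcome.

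The conclusion assumes that the article's outcome list reflects what is collected, and that the other-information item does not itself name the booklet. The increase from 174 to 215 or 272 depends on assumed exposure of 10% or 20% and on full effect in exposed controls; it is not an estimate for this trial. Recruitment, completion, withdrawal and the variability of the primary outcome are unaffected.

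**What to change.** 1. In the Quantitative assessment list, delete the bracketed restriction to the intervention group. Ask about booklet use in both groups at T1, T2 and T3 (any use, number of times, where obtained), placed within a list of information resources. Add the item to Table 1.
2. Report the proportion of controls who used the booklet, with a confidence interval, as a feasibility result, and acknowledge its imprecision.
3. Reconcile the Quantitative assessment list with the Quantitative data section, so that both state in which arms, and at which times, booklet use and other information use are collected and analysed.
4. Reword the use–outcome item as a descriptive tabulation within the intervention group, with no statement of influence, and keep the randomized contrast as the only between-group estimate.

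The cost is one extra item for controls on three postal questionnaires that are already planned. The downside is a small risk that naming the booklet prompts some controls to look for it; placing it within a list of resources limits that. Steps 1 and 2 address control exposure and step 4 addresses the use–outcome wording; neither substitutes for the other.

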#### Qualitative assessment

We will conduct semi-structured qualitative interviews at 20 weeks post-randomization, with a random sample of 15 patients and carers (or until data saturation), selected from both control and intervention groups, as well as all health professionals involved in the feasibility trial (n = 9). The semi-structured interviews will explore the feasibility and acceptability of the recruitment procedures (such as allocation, randomization and potential weaknesses of the design), use and perceived usefulness of existing resources and services, information and self-management support needs, perceived acceptability of the intervention and perceived barriers and facilitators to the use and dissemination of the intervention in routine care.

### Data collection and management

Data will be collected at baseline, four, 12 and 20 weeks post-randomization using a questionnaire and seizure diary completed by the carer, with the patient’s involvement whenever possible. The baseline questionnaire will be completed at the initial meeting with the research nurse. The follow-up questionnaires will be sent to the carer in the post and returned in a prepaid envelope. A research fellow will follow-up on patients and carers using the telephone at four, 12 and 20 weeks post-randomization to encourage the return of the questionnaires. A random sample of participants will also be invited to take part in an interview at 20 weeks post-randomization.

Data management will be provided by NRTU. The web-based data entry system will be built using Microsoft SQL Server tools. It will comply with the International Conference on Harmonization of Technical Requirements for Registration of Pharmaceuticals for Human Use Guideline for Good Clinical Practice (GCP), and will be restricted to authorized study team members and NRTU staff.

### Data analysis

#### Quantitative data

The analysis primarily aims to determine the feasibility of undertaking a full-scale randomized controlled trial and will seek to assess:The number and demographics of eligible patients identified, screened, consented and randomized to each arm, and the relative performance in each clinic.The demographics of patients who are excluded from the trial, reasons for exclusion and estimation of the proportion of eligible patients approached who agree to enter and complete the trial.The proportion of completed study measures in each arm, measured from baseline to the last follow-up assessment.The proportion of patients withdrawing from the study, measured from baseline to the last follow-up assessment.The variation in the primary outcome measure that will be used, following Cocks and Torgerson [32], to determine whether a one-sided 80% confidence interval would exclude a 10% increase in the primary outcome (ELDQOL).The frequency of use of the Books Beyond Words intervention, and other sources of information before and after randomization, and the extent to which use of the Books Beyond Words booklet influences outcome and other information resource use.

In parallel, a health economic assessment will be undertaken. We will monitor levels of resource-use and quality of life to inform the decision as to how costs and benefits should be measured as part of a future, more definitive study. NICE guidance recommends that costs are calculated from the perspective of the NHS and Personal Social Services (PSS) [33]. We will thereby seek to monitor levels of resource-use associated with the epilepsy booklet and the use of other NHS and PSS resource-items. Appropriate unit costs will subsequently be attached to all items of resource-use, to estimate the mean overall cost in each study-arm [34]. In line with NICE guidance, the EQ-5D [35] will be used to assess the effectiveness of each option. This will enable the quality-adjusted life year gain to be estimated. All analyses will be reported according to relevant CONSORT standards [36].

#### Qualitative data

The data collected in the semi-structured interviews will be analyzed using a two-step thematic content analysis derived from descriptive phenomenology [37, 38], assisted by the computer software NVivo.

### Sample size and feasibility of recruitment

The present study aims to assess the variation in the primary outcome measure between groups from baseline to the 12-week follow-up assessment, in order to determine whether the intervention is likely to achieve a 10% increase in the participants’ quality of life [32]. This would equate to an effect size of approximately 0.4, requiring a total sample size of 174 in a full study (1-β = 0.8, α = 0.05). Based on the requirement of 9% of the total sample size in each group, this indicates a required sample size of 16 per group, and will enable the exclusion of an effect size of <0. Given a potential 25% dropout rate, a sample size of 20 per group (40 participants in total) will be targeted. However, the study team, the selected study design and recruitment procedures will aim to minimize all potential dropouts whenever possible.

Recent audit data indicates that there were 196 patients with epilepsy and learning disabilities registered at the Hertfordshire Partnership University NHS Foundation Trust in May 2013. A preliminary screening exercise has already been undertaken by the lead consultant psychiatrist, at each epilepsy clinic, confirming that 112 out of 196 patients meet the study’s inclusion criteria. This does not include new referrals, who will be screened for eligibility once recruitment commences. The study will therefore aim to recruit approximately 36% of eligible patients.

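### The target of 20 per group does not cover the stated 25% dropout: it leaves 15 per group, one short of the plan's own requirement of 16 (a minor arithmetic correction).

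*Protocol article*

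**What the plan says.** The protocol article, under 'Sample size and feasibility of recruitment', builds the target in a short chain.

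- The full trial is sized first: "This would equate to an effect size of approximately 0.4", "requiring a total sample size of 174 in a full study (1-β = 0.8, α = 0.05").
- The feasibility sample is a fixed share of that total: "Based on the requirement of 9% of the total sample size in each group", and "this indicates a required sample size of 16 per group".
- Attrition is then added: "Given a potential 25% dropout rate, a sample size of 20 per group (40 participants in total) will be targeted".

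The section says that 16 per group will allow an effect size below zero to be excluded. It closes with an intention to keep dropout as low as possible, but gives no planning rate lower than 25%. The Abstract repeats the total of 40, and the recruitment fraction of about 36% of eligible patients is 40 out of 112. Under 'Data analysis', the criterion for the primary outcome is a one-sided 80% confidence interval.

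**The concern.** The requirement of 16, the dropout rate of 25% and the target of 20 stand in adjacent sentences, and the third is presented as following from the other two. It does not. A dropout rate is a share of those who enter the study, and the article uses that sense under 'Data analysis', where it plans to report the proportion of patients who withdraw. Applied to 20 per group, a 25% loss falls below 16.

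What is at stake is whether the headline sample size is stated correctly. Someone relying on this section would believe that the study can lose a quarter of its participants and still have the number it says it needs. It can lose only a fifth.

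**Working it through.** **Inputs**, from 'Sample size and feasibility of recruitment' unless noted:

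- full-trial total: 174
- share required in each feasibility group: 9%
- requirement per group: 16
- dropout: 25%
- target: 20 per group, 40 in total
- eligible patients: 112
- confidence criterion: one-sided 80% ('Data analysis')

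**1. The requirement reproduces.** 0.09 x 174 = 15.66, rounded up to 16 per group (32 in total).

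**2. The target reproduces only by multiplication.** 16 x (1 + 0.25) = 20.0. This adds a quarter of the required number. It does not allow for the loss of a quarter of those randomised.

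**3. Back-check.** 20 x (1 - 0.25) = 15 per group, or 40 x 0.75 = 30 in total. The shortfall is 1 per group and 2 overall. Fifteen is also below the unrounded 15.66.

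**4. The allowance that matches the stated rate.** n / (1 - d) = 16 / 0.75 = 21.33, so 22 per group and 44 in total. Then 22 x 0.75 = 16.5 expected per group.

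**5. Other ways of arriving at 20 and 40.**

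| Start | Calculation | Result |
|---|---|---|
| Unrounded requirement | 15.66 / 0.75 = 20.88 | 21 per group |
| Total requirement | 32 / 0.75 = 42.67 | 43 in total |

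Neither gives the stated target.

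**6. Dropout that 20 per group does cover.** 1 - 16/20 = 20%.

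**7. Effect on precision**, in standardised units with equal groups. The standard error is sqrt(2/n), the one-sided 80% half-width is 0.8416 x sqrt(2/n), and the lower limit is taken at an observed effect of 0.4.

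| Evaluable per group | Standard error | Half-width | Lower limit |
|---|---|---|---|
| 16 | 0.354 | 0.298 | 0.102 |
| 15 | 0.365 | 0.307 | 0.093 |

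The ratio of the half-widths is sqrt(16/15) = 1.033, about 3%. With the t distribution (30 and 28 degrees of freedom) the lower limits are 0.098 and 0.088. Zero is excluded in every case.

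**8. Chance of reaching the requirement**, assuming that each participant drops out independently with probability 0.25.

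| Randomised per group | At least 16 in both groups | At least 32 in total |
|---|---|---|
| 20 | 17% | 30% |
| 22 | 49% | 71% |

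**9. Recruitment fraction.** 40/112 = 36%, as stated. With 44 it would be 44/112 = 39%.

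**The case against.** The strongest reply is that nothing of substance depends on the difference between 15 and 16. This is a feasibility study. The article says that it will not show whether the intervention works, and no power claim for this study rests on the 16. The one property attached to that number, excluding an effect below zero, survives at 15 when 0.4 SD is observed. All of this stands and sets the severity. It does not make the sentence correct: nothing in the article says that 15 is acceptable, and the aim of minimising dropout is not a lower planning rate.

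A reader might go further than the documents allow in four ways.

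- **That the study loses the precision it promises.** It does not; the half-width widens by about 3%.
- **That a retention criterion is set wrongly.** The article contains no such criterion. Withdrawal is a quantity to be estimated, and 25% is only a planning allowance.
- **That the 17% and 30% chances measure the error.** They do so only in part. With 22 per group they become 49% and 71%, so chance variation remains even when the allowance is calculated properly, and the article promises no such probability.
- **That the shortfall can be dismissed because the pilot-size rule needs far fewer than 16.** The article states the rule as 9% of the total in each group, which gives 16. A smaller requirement cannot be derived from the text at hand.

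**Conclusion.** Wrong as written, and minor. On the article's own figures, 20 per group with 25% dropout gives 15 evaluable per group, one short of the stated 16 (30 against 32 in total). Twenty per group is enough for 20% dropout; 25% would need 22 per group, 44 in total.

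The conclusion rests on two readings: that 16 is the number needed after dropout, which is why an allowance is added to it, and that the 25% applies to those randomised. It takes the requirement of 16 as stated and does not depend on how the 174 was obtained. The precision figures also assume equal groups, and the lower limits assume an observed effect of 0.4 SD. The error lies in the stated figure; it gives no ground for doubting that the study can meet its feasibility aims.

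**What to change.** Keep 40 participants and rewrite the one sentence in either of two ways:

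- 40 randomised allows for 20% dropout, leaving 16 evaluable per group; or
- 40 randomised with 25% dropout gives 15 evaluable per group, with precision quoted for 15 (standard error 0.365, one-sided 80% half-width 0.307 SD).

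Both leave the total in the Abstract and the 36% recruitment fraction unchanged. The first replaces the 25% planning rate, so it should be chosen only if 20% is a rate that the team can defend; otherwise the second is the plainer statement. If the sponsor prefers to hold both 16 and 25%, the consistent target is 44, and the Abstract and the recruitment fraction (39%) would have to change with it.

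Keeping 40 costs one sentence and a slightly less favourable stated figure, with no change to conduct or analysis.
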